During the first 6 months (prior to the baseline period [Phase 1]), Drs. [name] and [name] will travel to each of the 6 hospitals selected for Aim 2 and oversee a qualitative process evaluation of hand hygiene practices. The evaluation will include observations on individual units, semi-structured interviews with IC staff and leadership, and focus groups with staff on one high and one low performing unit at each hospital. Semi-structured interviews will be conducted individually with the IC team at each site, as well as site leadership. (See Appendix for Interview Guide.) The IC team includes the hospital epidemiologist, Infection Control Professional (ICP), and MRSA/MDRO Coordinator. Leadership will include those who oversee the IC team and nurse managers of the high and low performing units. The questions will focus on the history of infection control at the hospital (e.g., changes in personnel, gaps in staffing IC positions, integration of the MRSA Program, etc.), descriptions of how hand hygiene data are collected, goals for hand hygiene compliance, current interventions to promote hand hygiene, and plans to meet Joint Commission's National Patient Safety Goal for hand hygiene. The qualitative research team will also go on infection control rounds with the IC team with particular focus on the wards/units included in the study. The qualitative team will ask the IC team to describe what they look for during infection control rounds and identify barriers and facilitators to IC on each unit. The qualitative team will then return to those units to record hand hygiene specific data such as number and placement of hand hygiene dispensers, number and placement of hand hygiene signs, and whether and how hand hygiene compliance data are displayed on the unit and/or reported back to the staff. Field notes from both observation periods will be recorded.

The qualitative team will then conduct focus groups with the lowest and highest performing units at the hospital. (See Appendix for Focus Group Guide.) The focus groups will cover questions on knowledge of hand hygiene guidelines, the unit's interactions with IC, and current and past interventions to try to improve compliance. The qualitative team will return to Iowa City to analyze the data and develop case studies of each hospital's hand hygiene practices, including compliance data collected for the study. This will serve as a baseline description of the "hand hygiene culture" of each facility.

After each interventional phase is implemented, semi-structured interviews will be conducted over the phone with the IC team and nurse managers at each hospital (during the washout periods and during the post-intervention qualitative evaluation). The interviews will focus on perceived barriers and facilitators to implementation, staff reaction to the strategies, perceived impact on workflow and patient/provider relationships, and perceptions of each intervention's fit with the culture of the hospital.

Toward the end of Phase 6, Drs. [name] and [name] will return to the sites and replicate the same qualitative evaluation protocol. The qualitative evaluation will identify changes in "hand hygiene cultures" and document feedback about the interventions from frontline staff during unit focus groups.

All interviews will be audiorecorded on digital encrypted recorders or over the phone directly to a secure server. They will then be transcribed by in-house transcribers and reviewed for accuracy. All textual data (field notes and transcripts) will then be imported into MAXQDA, a qualitative data management and analysis software program.

## **Risk protection**

### AIM I:

With regards to observations of hand hygiene compliance, no individual identifying information will be collected from healthcare workers or patients. Data regarding MRSA and hospital-acquired infection rates will be collected from the VA database, IPEC. All data will be collected anonymously. There is no patient-level data for the observation portion of the study; healthcare worker data will be anonymously observed and then aggregated. Removal of access to research study data will be accomplished for study personnel when they are no longer part of the research team and any incidents involving theft of data, etc., will be reported immediately. MRSA and hospital-acquired infection outcome data will be analyzed using VA datasets. Given the number of veterans included in this retrospective analysis and the use of existing data, informed consent will not be obtained from patients. This practice is consistent with practices for studies that use existing administrative data and medical records data. However, our data management protocol will ensure the protection of the protected health information thereby minimizing risks to individual veterans. A waiver of consent is included.

Risk will be minimized by limiting access to data, maintaining study paper files in locked offices, and storing data on password-protected computers and on servers, which are secured in locked

rooms by the Iowa City VA Medical Center Office of Information Resources Management. The servers can only be accessed by individuals with OIT-created network accounts. Data will be secured using network directory permissions assigned by OIT at the direction of the PI; thus ensuring that only study personnel with the approval of the PI (per IRB requirements) have access to identifiable human subject data. Data collection, management, and analyses will be compliant with VA data use agreements. In addition, reports of study findings will not identify individual HCWs.

The servers can only be accessed by individuals with IRM-created network accounts. Data will be secured using network directory permissions assigned by IRM at the direction of the PI; thus ensuring that only study personnel with the approval of the PI (per IRB requirements) have access to identifiable human subject data. Data collection, management, and analyses will be compliant with VA data use agreements. In addition, reports of study findings will not identify individual patients.

AIM 2:

VA Infection Control (IC) Team and Leadership: For six designated sites, a site visit will be coordinated with the Site PI assistance. Each member of the IC Team will be emailed a letter of invitation from the PI of the proposed research project. The letter will contain elements of consent. The PI or a member of her study team will then review the letter before conducting an interview with any member of the IC team. Site visits will take place during the baseline period and at the end of the interventions.

Four designated sites will not participate in site visits, but will participate in phone interviews with at baseline and post-intervention. Each member of the IC Team will be emailed a letter of invitation from the PI of the proposed research project. The letter will contain elements of consent. The PI or a member of her study team will then review the letter on the phone before conducting an interview with any member of the IC team.

In addition, phone interviews will be conducted at all 10 sites during the washout periods to gather any feedback from the IC team on implementation barriers for the previous intervention conducted at their site.

VA Healthcare Workers (HCWs): With assistance from the Site PI, the Iowa City Research Coordinator will contact the appropriate supervisors and inform them of the Qualitative Team's site visit. She will arrange a time for the focus group on two different units. At the time of the focus group, participants will be given an informational sheet and the PI will review the elements of consent (see focus group script with elements of consent and information sheet) with the participants in the focus group. They will be given the opportunity to ask questions and have all their questions answered. Participation in the focus group will be an indication of consent. This consent process has worked well in other focus group projects the team as conducted.

Data Collection: The study personnel will be responsible for reviewing elements of consent before each point of data collection.

Interviews and focus groups will be recorded on encrypted recorders and files will be uploaded directly to a secure server. Recordings will be transcribed and reviewed for accuracy. All data (recordings, transcripts) will be stored on a secured server. Each participant will be assigned a unique study identifier which will be used on all data. Subject identities (e.g., names, addresses, professional title) will be kept separate from the data and linkage information will only be available to the PI and Research Coordinator.

For proposed research, confidentiality risk will be minimized by limiting access to data to study personnel, removing unique participant identifiers (e.g., names) from analytical files, maintaining study data forms and files in locked offices, and storing study databases on password-protected computer files housed on a secure server. This server is configured and maintained by VA IRM staff and meets all VA security standards. The server is in a secure location at the Iowa City VAMC, where it is in a video-monitored area behind locked doors. All analyses will be performed on data in which unique patient information has been replaced with study identification numbers to protect confidentiality. A list matching names and identification numbers will be stored in the secure server. The crosswalk data file will be accessible only to the PI and Research Coordinator.

The proposed research project does not involve the collection of biological specimens.

## **5.2 Recruitment Methods**

### AIM 1:

All veterans admitted to acute care at the 10 VA medical centers during the study period will be included in this retrospective data analysis. Approximately 135,852 veterans will be included regardless of age, race, gender, or underlying health status. Additionally, women and minorities will be included in this study.

The hand hygiene behavior of all facility staff working on the wards/ICUs during the periods of hand hygiene observation will be recorded.

This study aim will not use any recruitment materials nor will subjects be paid.

### AIM 2:

VA Infection Control (IC) Teams: Approximately 18 hospital epidemiologists, Infection Control Professionals, and MRSA/MDRO Coordinators will be asked to participate in the study through in-person and phone semi-structured interviews (3 members of the IC team from 6 sites). Hospital epidemiologists, Infection Control Professionals, and MRSA/MDRO Coordinators from 4 additional sites will be asked to participate in the study through phone interviews (approximately 12 study participants, 3 members of the IC team from 4 sites). The hospital epidemiologist is a Site PI on the study and will facilitate introductions to the IC team. The IC team will be asked to participate because of the unique knowledge they have regarding how hand hygiene is currently monitored and promoted at each VA facility and may have unique

insights into the barriers and facilitators of implementation. The participants may not be veterans, but are important to the study due to role as VA practitioners.

VA Healthcare Workers (HCWs): Approximately 140-150 healthcare workers (facility, leadership, nurses, physicians, respiratory therapists, dieticians, etc.) will be asked to participate in the study through in-person individual and group interviews. Approximately 24 will be from facility leadership. We anticipate approximately 6 participants per focus group. Two focus groups will be conducted on different units within each of 6 VA facilities. Healthcare workers may or may not be veterans; however, their participation in the study is important as they will provide crucial insight into how hand hygiene is practiced at their facility and barriers and facilitators to the interventions being implemented in the study.

We will use email letters and informational sheets to assist in recruiting HCWs for individual and semi-structured interviews and focus groups for Aim 2. Participants will not be paid.

### **5.3 Informed Consent Procedures**

We will request a waiver of informed consent for all parts of the study except the semi-structured interviews (Aim 2). For Aim 2, we will request waiver of documentation of informed consent.

Aim 2 consists of HCW semi-structured interviews. All participants will receive information in both oral and/or written form regarding the risk and benefits of the project, confidentiality procedures, and study personnel to contact regarding questions and concerns (including contact numbers for the Central IRB). The PI or members of the study team will be responsible for reviewing elements of consent before each point of data collection. Participants will be given the opportunity to ask questions and have all their questions answered. Participation in the interview will be an indication of consent.

All interviews will be conducted by the Iowa City Qualitative Team and consent procedures will be conducted by [name] or the Iowa City study team. No investigators/research assistants from local sites will be performing interviews or consent procedures.

### **5.4 Inclusion/Exclusion Criteria**

#### AIM 1:

All veterans admitted to acute care at the 10 VA medical centers during the study period will be included in this retrospective data analysis. Approximately 135,852 veterans will be included regardless of age, race, gender, or underlying health status. Additionally, women and minorities will be included in this study.

The hand hygiene behavior of all facility staff working on the wards/ICUs during the periods of hand hygiene observation will be recorded.

#### AIM 2:

VA Infection Control (IC) Teams: Approximately 50 hospital epidemiologists, Infection Control Professionals, and MRSA/MDRO Coordinators will be asked to participate in the study through in-person and phone semi-structured interviews (3 members of the IC team from 6 sites). Hospital epidemiologists, Infection Control Professionals, and MRSA/MDRO Coordinators from 4 additional sites will be asked to participate in the study through phone interviews. The participants may not be veterans, but are important to the study due to role as VA practitioners.

VA Healthcare Workers (HCWs): Approximately 150 healthcare workers (facility, leadership, nurses, physicians, respiratory therapists, dieticians, etc.) will be asked to participate in the study through in-person individual and group interviews. We anticipate approximately 6 participants per focus group. Two focus groups will be conducted on different units within each of 6 VA facilities. Healthcare workers may or may not be veterans.

## 5.5 Study Evaluations

Participants will not be required to complete any procedures as part of the study. The only evaluation that some participants will participate in are semi-structured interviews among VA staff.

## 5.6 Data Analysis

### AIM 1:

Sample Size: We will collect continuous baseline data from each unit during the 6 month period prior to intervention. We estimate that 10-14 observations/hour can be witnessed based on our previous studies. Taking the lower estimate of 10/hour and assuming 60 hours/month of observation per site for a total of 600 hours/month projects to 36,000 observations during the 6 months pre-intervention period. (See Project Gantt Chart.) These will be spaced by unit and day/night shift as mentioned above. Given the 59 wards/ICUs, we will have an average of 120 directly observed hand hygiene episodes in each unit/month.

*Power Calculation*: Using our primary outcome, we estimated hand hygiene rates for each phase of the study. Given 30,000 observations in the group randomized to the intervention and in the group randomized to the control, each phase of the study will have 99% power to detect a 5% increase in hand hygiene rates due to the intervention (e.g., 60% to 65%). (See Table 2.)

Table 2. Power Calculations for Each Phase of Study

|         | Baseline Hand Hygiene Rate | Power to Detect a 5% Increase in Hand Hygiene Rate |
|---------|----------------------------|----------------------------------------------------|
| Phase 2 | 60%                        | 99%                                                |
| Phase 4 | 65%                        | 99%                                                |
| Phase 6 | 70%                        | 99%                                                |

Analysis: Following methods we have outlined previously, we will use quasi-Poisson mixed effects models to account for matching and the cluster-randomization design, as observations over time within individual rooms, units and hospitals are expected to be correlated. The

dependent variable in each model will be the monthly hand hygiene compliance rate. The numerator will be the number of times a HCW disinfects their hands while the denominator will be the number of opportunities for hand hygiene. The ideal denominator is the WHO 5 Moments of Hand Hygiene and where possible, we will collect these data. However, our current IIR 09-099 suggests that the most reliably measurable moments are room entry and room exit. Separate models will be run for the WHO 5 moments (combined as one dichotomous measure and for each of the individual “moments”), room entry compliance, and room exit compliance. Independent variables will include the tested intervention, the bed size and type of unit, monthly census, estimated monthly nurse to patient ratios, and other known confounders associated with hand hygiene compliance. The results will advance understanding of the effectiveness of individual interventions and their combined effectiveness as a bundle.

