Phase 1 will obtain baseline rates of hand hygiene compliance and MRSA on each unit at each hospital. Phase 2 will compare different strategies for changing hand hygiene signage on hospital units to determine if periodically varying signage more effectively modifies hand hygiene behavior than using static environmental cues. The 59 individual hospital units will be randomized to 3 groups (~19 units per group): 1) no change in signs; 2) changing signs monthly; and 3) changing signs weekly. To improve power, we will use stratified randomization with matching based on baseline hand hygiene compliance rates during Months 1-6. Block randomization will be used to ensure that baseline compliance rates will be evenly distributed across conditions. To do this, we will rank the units by compliance rate and then randomize by blocks of three using a computer-generated list of random numbers prepared by the Data Manager in consultation with the biostatistician. During Phase 3, the sign change strategy that was associated with the highest hand hygiene compliance will be universally implemented in the 59 study units in all 10 hospitals, this will set a new baseline and serve as a wash-out period. In our current study of hand hygiene interventions, we were able to detect a difference within six weeks. Thus, 3 months is likely enough time for wash-out.

Phase 4 will compare the additional benefits of the other 2 interventions—distribution of individual hand sanitizers to healthcare workers and obtaining cultures of healthcare workers' hands with visual feedback on hand contamination. In Phase 4, hospitals will be randomized to 3 groups: 1) signage only (4 hospitals); 2) signage and hand sanitizers (3 hospitals); and 3) signage and hand cultures (3 hospitals). Group assignment will again be stratified using block randomization (4, 3, 3), based on hand hygiene compliance rates measured during Phase 3. Individual strategies will be randomized by hospital to decrease contamination between wards/units. During Phase 5, the Phase 4 intervention associated with the highest compliance rates will be universally implemented; if both interventions were equally efficacious, the signage only hospitals will be randomized to receive either the hand sanitizer or hand culture intervention. Phase 5, like phase 3 will also serve as a washout period. Phase 6 will determine the potential incremental benefits of all 3 interventions in combination by re-randomizing

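### The power calculation assumes 30,000 observations per group, but the stated observer hours give about 10,800 to 18,000 per arm at the adopted 10/hour and at most 25,200 at 14/hour

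*Protocol*

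**What the plan says.** Section 5.6 (Data Analysis, Aim 1, Sample Size) gives a range for the observation rate: "We estimate that 10-14 observations/hour can be witnessed based on our previous studies". It adopts the lower end and continues: "assuming 60 hours/month of observation per site for a total of 600 hours/month projects to 36,000 observations during the 6 months pre-intervention period". From this it derives a monthly figure per unit: "Given the 59 wards/ICUs, we will have an average of 120 directly observed hand hygiene episodes in each unit/month".

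The Power Calculation paragraph that follows uses a different number: "Given 30,000 observations in the group randomized to the intervention and in the group randomized to the control". On that basis it claims 99% power in each phase for a 5-point rise in compliance. Table 2 repeats the 99% for Phases 2, 4 and 6, with baseline rates of 60%, 65% and 70%.

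The allocation is in section 5.1 (Study Procedure). Phase 2 randomizes the 59 units to three groups. Phase 4 randomizes the hospitals as follows: "1) signage only (4 hospitals); 2) signage and hand sanitizers (3 hospitals); and 3) signage and hand cultures (3 hospitals"). Phase 6 re-randomizes the ten hospitals five to five. The Project Gantt Chart gives each of these phases six months (months 13-18, 22-27 and 31-36).

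**The concern.** The 36,000 is a total over all sites and therefore over all arms. Two groups of 30,000 would need 60,000 observations from a phase that is projected to supply 36,000, and in Phases 2 and 4 there is a third arm to fill as well. The 30,000 is the only sample-size input given for Table 2, so the table describes a trial larger than the stated observer hours can deliver.

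The unit-month average is a second, smaller mismatch. It follows directly from the 10-per-hour projection but does not agree with it. It matters because the dependent variable in the planned models is the monthly compliance rate.

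**Working it through.** **Inputs.** Rate 10 per hour, range 10 to 14; 60 hours per month at each of 10 sites, so 600 hours per month; 59 units (all section 5.6). Arms: three groups of units (Phase 2), 4/3/3 hospitals (Phase 4), 5/5 hospitals (Phase 6) (section 5.1). Six months per phase (Gantt Chart).

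**Assumption.** Section 5.6 states the hours for the pre-intervention period only. Section 5.1 says compliance is collected monthly throughout for all 59 units, but gives no hours for later phases. I carry the baseline hours forward.

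**Step 1: the plan's own total.** 10 × 600 × 6 = 36,000. This reproduces.

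**Step 2: observations per arm in a six-month phase.** Each hospital supplies 60 × 10 × 6 = 3,600 at 10/hour and 60 × 14 × 6 = 5,040 at 14/hour.

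| Phase | At 10/hour | At 14/hour | Rate needed for 30,000 per group |
|---|---|---|---|
| 2 (three arms) | 36,000/3 = 12,000 | 50,400/3 = 16,800 | 90,000/3,600 = 25/hour |
| 4, four hospitals | 4 × 3,600 = 14,400 | 4 × 5,040 = 20,160 | |
| 4, three hospitals | 3 × 3,600 = 10,800 | 3 × 5,040 = 15,120 | 30,000/(0.3 × 3,600) = 27.8/hour |
| 6 (five hospitals) | 5 × 3,600 = 18,000 | 5 × 5,040 = 25,200 | 60,000/3,600 = 16.7/hour |

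At 10/hour the stated 30,000 is too large by a factor of 30,000/18,000 = 1.7 to 30,000/10,800 = 2.8. At 14/hour the factor is 30,000/25,200 = 1.2 to 30,000/15,120 = 2.0.

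The Phase 2 figure is an average. Units are randomized, hours are fixed by site, and Table 1 lists from 3 to 11 units per site. If a site divides its hours equally among its units, a unit receives between 600/11 = 55 and 600/3 = 200 observations per month at 10/hour, so an arm's total depends on which units it draws.

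**Step 3: unit-month average.** 10 × 600/59 = 6,000/59 = 101.7. The stated 120 is 18% higher. At 14/hour the average is 8,400/59 = 142.4. A value of 120 needs 120 × 59/600 = 11.8 per hour.

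**Step 4: effect on power if observations were independent.** The protocol gives no significance level; I assume two-sided 5%. For 60% against 65%, 99% power needs (1.96 + 2.326)² × (0.24 + 0.2275)/0.05² ≈ 3,435 per arm. With pooled variance the three Table 2 rows need 3,440, 3,220 and 2,926. Every per-arm count in the table above exceeds these.

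**The case against.** **Power is not affected.** Under independence this stands: 10,800 per arm already gives more than 99.9% power for each row of Table 2, so correcting the counts changes no entry. But section 5.6 (Analysis) itself expects observations within rooms, units and hospitals to be correlated, and the power paragraph states no intracluster correlation or design effect. The independence result therefore does not settle what power the trial has.

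**The 120 is attainable.** This also stands. It needs 11.8 per hour, inside the protocol's 10 to 14. It conflicts with the rate the paragraph adopts, not with every rate in the document. A reader might infer that both planning figures are impossible; that is true of the 30,000 only.

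**The 30,000 might pool phases.** Adding the preceding baseline or washout phase at 10/hour gives 24,000 (Phase 2), 21,600/16,200/16,200 (Phase 4) and 27,000 (Phase 6), all short. At 14/hour it gives 33,600, 30,240/22,680/22,680 and 37,800, so the three-hospital arms still fall short. Another possible origin is the 30-month trial: 30 × 6,000 = 180,000, divided by three phases and two groups, is 30,000. That would count baseline and washout months as data from randomized groups. The protocol describes neither device.

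**Later phases might have more observer hours.** No passage says so. This is why the per-arm counts have to be labelled as resting on the baseline hours.

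**Conclusion.** The point holds. The 30,000 per group cannot be reconciled with 36,000 per six months over all arms, and no rate the protocol states reaches it in any phase. The expected counts are 10,800 to 18,000 per arm at 10/hour and 15,120 to 25,200 at 14/hour, assuming that the baseline observer hours continue and, for Phase 2, reading the figure as an average. The 120 per unit-month is a minor inconsistency with the adopted rate.

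A reader might go further and infer that true power is well below 99%. The documents do not support a figure. Suppose, purely as illustration, that the 99% at 30,000 already absorbed a design effect of 30,000/3,440 = 8.7 in Phase 2. Holding that constant, power at 12,000 would be about 77%. But the number of units is fixed, so fewer observations per unit also reduce the design effect. With 59/3 = 19.7 units per arm, 30,000 means 1,525 per unit and an implied correlation of (8.72 - 1)/1,524 = 0.005. At 12,000 there are 610 per unit, the design effect is 1 + 609 × 0.00506 = 4.1, the effective size is about 2,940 and power is about 98%. The answer depends entirely on a correlation and a clustering structure that the power calculation does not give. What is established is that Table 2 rests on a per-group size that the design does not deliver.

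**What to change.** In section 5.6:

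- Replace the 30,000 with expected per-arm counts for each phase: about 12,000 (Phase 2), 14,400/10,800/10,800 (Phase 4) and 18,000 (Phase 6) at 10/hour, with the 14/hour values as the upper end. Label them as averages under the stated observer hours. If more hours are planned for the intervention phases, state them and derive the counts from those.
- Replace 120 per unit-month with about 102, or state the rate that gives 120 (about 11.8 per hour).
- Recompute Table 2 from the corrected counts with allowance for clustering by unit in Phase 2 and by hospital in Phases 4 and 6, stating the assumed correlation and a range around it.

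The cost is a wording change and one recalculation. The count correction by itself requires no change to design, allocation or data collection.

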they pose to their patients. Photographs of the hand cultures will be displayed in common staff areas, but out of patient view. During the initial site visits, the qualitative team will observe current feedback mechanisms on the wards and units and work with the IC team to plan a way of displaying the feedback. This information will be used in interviews and planning sessions conducted with the four sites the qualitative team does not visit. Since the collected of culture plates is an intervention and not being done for data collection purposes, all culture plates will be destroyed via proper disposal techniques and digital photographs of the culture plates will be used for educational purposes only.

Study Procedure: The trial will entail 6 phases. (See Figure 3.) As an overview, Phases 2, 4 and 6 will be intervention periods and Phases 3 and 5 will establish a new baseline and serve as washout periods. Importantly, Phase 2 randomization will occur at the ward/ICU level since our pilot data suggests room entry signs can be randomized at the ward/ICU level. However, to avoid crossover effects, the other interventions will be randomized at the hospital level in Phases 4 and 6.

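### The 99% power stated for Phases 2, 4 and 6 ignores clustering and holds only while the residual spread between units or hospitals stays below thresholds the protocol never states

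*Protocol*

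**What the plan says.** The Power Calculation in section 5.6 has one sample-size input: "Given 30,000 observations in the group randomized to the intervention and in the group randomized to the control". From this it concludes that "each phase of the study will have 99% power to detect a 5% increase in hand hygiene rates due to the intervention", with 60% to 65% as the example. Table 2 repeats 99% for Phase 2 (baseline 60%), Phase 4 (65%) and Phase 6 (70%). No number of clusters, intra-cluster correlation (ICC), between-cluster SD, design effect or significance level goes with it.

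The Analysis paragraph that follows plans mixed-effects models for the cluster design because "observations over time within individual rooms, units and hospitals are expected to be correlated".

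Section 5.1 (Study Procedure) sets the randomisation. In Phase 2 the 59 units are split into three groups of about 19. After that, "the other interventions will be randomized at the hospital level in Phases 4 and 6". The Phase 4 groups hold 4, 3 and 3 hospitals, and the two Phase 6 groups hold 5 each.

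The Sample Size paragraph in section 5.6 projects 36,000 observations over six months across all ten sites.

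**The concern.** In a cluster-randomised comparison the information comes mainly from the number of randomised clusters and how much they differ from one another. Extra observations within a cluster shrink only the sampling part of the variance. The analysis plan recognises this and the power calculation does not, so the two halves of one section disagree.

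Phases 4 and 6 are the most exposed, with three to five hospitals per arm. They carry the trial's main question of whether adding interventions improves compliance. If a phase is described as having 99% power, a reader may take a small or null difference as strong evidence that the added component does nothing. With few hospitals, the same result could simply reflect low power.

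**Working it through.** **Inputs from the protocol.** Baselines are 60%, 65% and 70%, and the difference is 5 points (Table 2 and text). The stated size is 30,000 per group. The projected 36,000 observations per six months gives 36,000/10 = 3,600 per hospital and 36,000/59 ≈ 610 per unit. Clusters per arm are about 19–20 units (Phase 2), 4 v 3 hospitals (Phase 4, control v one active arm) and 5 v 5 hospitals (Phase 6).

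**Assumptions.** Two-sided alpha 0.05; the observation rate of the pre-intervention period continues; between-cluster SD is varied because none is given.

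**1. Reproducing the stated figure.** Treat all observations as independent. For 60% v 65%, SE = √[(0.24 + 0.2275)/30,000] = 0.00395, and 0.05/0.00395 = 12.7. Power exceeds 99.99%, and likewise for 65% v 70% and 70% v 75%. Exactly 99% would need only 3,440, 3,220 and 2,926 observations per arm. The stated figure therefore fits a calculation on independent observations.

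**2. The 30,000 is not what drives the problem.** At the projected rate each arm gets 36,000/3 = 12,000 observations (Phase 2), 3 × 3,600 = 10,800 to 4 × 3,600 = 14,400 (Phase 4) or 5 × 3,600 = 18,000 (Phase 6). That conflicts with 30,000 per group. Even so, 10,800 independent observations per arm still give more than 99.99% power.

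**3. Cluster-level power.** The variance of a cluster mean is SD² + p(1−p)/m, with m = 3,600 or 610. The SE of the difference is √(v₁/n₁ + v₂/n₂). Power comes from the noncentral t distribution with noncentrality 0.05/SE.

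- Phase 4, SD 3 points: v₁ = 0.0009 + 0.2275/3,600 = 0.000963; v₂ = 0.0009 + 0.21/3,600 = 0.000958; SE = √(0.000963/4 + 0.000958/3) = 0.0237; noncentrality 2.11. Power is 40% with 5 degrees of freedom (two arms) and 45% with 7 (all three arms pooled).
- Phase 6, SD 3 points: v₁ = 0.000958; v₂ = 0.0009 + 0.1875/3,600 = 0.000952; SE = √[(0.000958 + 0.000952)/5] = 0.0195; noncentrality 2.56. Power is 61% with 8 degrees of freedom.
- Phase 2, unit SD 5 points, 19 v 20 units: v₁ = 0.0025 + 0.24/610 = 0.00289; v₂ = 0.0025 + 0.2275/610 = 0.00287; SE = 0.0172; noncentrality 2.91. Power is 81–82%.

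| Residual between-cluster SD (points) | Phase 2 (units) | Phase 4 (hospitals; 5 / 7 df) | Phase 6 (hospitals) |
|---|---|---|---|
| 1 | >99% | 98% / 99% | >99% |
| 2 | >99% | 69% / 74% | 90% |
| 3 | 99% | 40% / 45% | 61% |
| 5 | 81–82% | 19% / 20% | 28% |
| 8 | 46% | 10% / 11% | 14% |
| Largest SD giving 99% | about 3.0 | about 0.9 / 1.0 | about 1.4 |

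**4. More observations do not repair it.** With the protocol's 30,000 per arm and SD 3 points, power is 41% in Phase 4 (5 df) and 62% in Phase 6.

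**5. Cross-check by design effect.** At an ICC of 0.01 the design effect is 1 + 3,599 × 0.01 = 37. Effective sizes are 10,800/37 ≈ 292 and 18,000/37 ≈ 487 per arm. Power is about 25% (Phase 4, taking 3 hospitals per arm) and 42% (Phase 6), before any penalty for few degrees of freedom.

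**The case against.** The strongest reply is that the design reduces the spread that matters. Phase 2 is stratified and matched on baseline compliance, Phase 4 is stratified on Phase 3 compliance, and the model is meant to account for matching. This has force. Take a raw hospital SD of 3 points and an assumed between-period correlation of 0.9. The residual SD is 3 × √(1 − 0.81) = 1.3 points, and baseline adjustment brings Phase 6 to about 99% and Phase 4 to about 89–94%, depending on degrees of freedom. With a raw SD of 5 and the same correlation, the figures are about 84% and 57–66%. But the power section claims no such gain, section 5.6 does not name baseline compliance as a covariate, and no stratification is described for Phase 6.

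A second reply is that 99% may hide an allowance for clustering, since independence gives more than 99.99%. A design effect of 30,000/3,440 = 8.7 to 30,000/2,926 = 10.3 would give exactly 99%. Nothing in the text indicates one. In Phase 6, with 6,000 observations per hospital, it would imply an ICC of only (10.3 − 1)/5,999 ≈ 0.0015.

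A reader might infer that 99% is out of reach at any plausible hospital spread, or that true power is probably well below one half. The documents support neither. No hospital SD is given, 99% is reached at small SDs, and Phase 6 keeps 90% at SD 2. The only documentary evidence on spread is the pilot under Preliminary Studies, where groups of 6 and 5 wards differed at baseline by 4.8 points (entry) and 3.9 points (exit). Dividing by √(1/5 + 1/6) gives crude SDs of 7.9 and 6.4. These are raw ward-level figures, each from a single contrast on the same wards, so they are only indicative and do not measure residual hospital spread.

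Finally, section 5.1 carries forward the strategy with the highest compliance, not one that passes a test. The stated power therefore does not operate the selection after Phases 2 and 4. It affects how the comparisons are interpreted.

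**Conclusion.** The point stands as a threshold. The 99% in Table 2 treats observations as independent in a trial that randomises units and hospitals, and it contradicts the correlation acknowledged in the same section. It is an error of method; the arithmetic reproduces.

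The claim fails above the SDs in the last row of the table: about 0.9 to 1.0 points between hospitals in Phase 4, 1.4 in Phase 6, and 3 between units in Phase 2. Phase 2 is the least affected. These figures rest on two-sided 0.05, 3,600 observations per hospital (about 610 per unit) and a t-test on cluster means. The SD is residual, after whatever stratification or adjustment achieves. How far actual power falls short cannot be determined from the protocol.

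**What to change.** Withdraw the 99% and replace Table 2 with cluster-based power for each phase, stating:

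- randomised clusters per arm;
- observations per cluster consistent with 36,000 per six months over all sites, in place of 30,000 per group;
- a between-unit and a between-hospital SD or ICC, taken from the existing direct-observation study and updated from Phase 1;
- alpha and t-based degrees of freedom;
- any credit for matching or baseline adjustment, with the assumed correlation, and baseline compliance named in the model if that credit is taken;
- the detectable difference at 80% power. At a residual hospital SD of 3 points this is about 7.7 points in Phase 4 (7 df; 8.3 with 5 df) and 6.3 in Phase 6.

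The cost is a recalculation and a change of protocol wording. No extra sites are needed. The downside is a less favourable stated power, most visibly in Phase 4.
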